**Method:**

**Study design:** Double blind, randomized placebo controlled clinical trial Phase III.

The study will be conducted on patients with COVID 19 infection for 4 weeks.

**Study setting:** The study will be conducted in Khartoum Isolation centers and Soba hospital Khartoum State Sudan

**Sample size:** All Patients who presented to Gabra and Soba hospital and confirmed with COVID 19 during the study period will be included after satisfying the inclusion criteria

**Study population:** (inclusion and exclusion criteria)

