**Randomization and blinding:**

The subjects, after stratification by age and sex, will randomly assigned to receive coded and indistinguishable Gum Arabic or placebo. Randomization will be conducted by using a sequence of computer-generated random numbers by independent individual.

Each participating center will be assigned a special code generated by the computer. The

randomization will be kept by the PI and a research assistant. The assessor for clinical outcomes would be blinded to the randomization status. The research staffs who perform the intervention would not know the assessment results. After the eligibility assessment by viral screening, laboratory and clinical assessments would be conducted at the baseline (after completion of informed consent), at first, second and 4th week

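### The allocation list is kept by the PI and a research assistant, so concealment and their own blind are not protected as the double-blind design requires

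*Protocol*

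**What the plan says.** The Method section describes the trial as "Double blind, randomized placebo controlled clinical trial Phase III".

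The section on randomization and blinding contains these statements:

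- Generation: the assignment is produced "by using a sequence of computer-generated random numbers by independent individual".
- Custody: the "randomization will be kept by the PI and a research assistant".
- Product: after stratification by age and sex, patients are "randomly assigned to receive coded and indistinguishable Gum Arabic or placebo". Each centre also receives its own computer-generated code.
- Assessor: "The assessor for clinical outcomes would be blinded to the randomization status".
- Staff giving the product: "The research staffs who perform the intervention would not know the assessment results".

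The secondary outcomes are clinical improvement with hospital discharge, and time to discharge after recovery.

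**The concern.** Generating a sequence independently protects a trial only if the people who recruit and manage patients cannot see it. Here the protocol separates generation from the study team and then gives custody back to two of its members. This is a positive statement of procedure, so it is not a gap that a statistical analysis plan could be expected to fill. Nor could such a plan repair the damage once patients have been assigned.

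Two things are at stake. At entry, anyone who can see the coming assignment can, knowingly or not, influence who is approached or consented next. After entry, anyone who knows the arm can let it colour care, the record of improvement or the timing of discharge.

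**Working it through.** No arithmetic applies. The protocol gives no sample size, effect size, standard deviation or power, so there is no figure of its own to reproduce. The check sets its statements side by side.

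1. **Who could know the allocation?** The person who generates the sequence, and the two people who keep it. No sealed, central or pharmacy release of assignments is described that would stand between the keepers and the list.

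2. **Who is stated not to know it?** Of the staff, only the assessor of clinical outcomes. The sentence on staff who give the intervention concerns a different matter: they are kept from the assessment results, not from the allocation. Patients are covered indirectly, by the coded and matching product.

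3. **Are the two keepers kept away from the places where knowledge matters?** The text shown neither says that they screen, enrol, dispense or treat, nor excludes it. A PI and a research assistant are members of the study team, so the protection would need to be written down.

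4. **Where could knowledge act?**
   - Entry: eligibility is wide (PCR-confirmed infection, age 8 to 90, either sex, three exclusions). The criteria are mostly objective, but enrolled patients may differ greatly in prognosis, and there is discretion in approach and consent.
   - Outcome: improvement and discharge are partly matters of judgement, and blinding one assessor does not blind those who manage the patient. The primary outcome is a change in an immune-response score. The planned investigations are laboratory tests and so less open to judgement, although the score is not defined.

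5. **Do the statements fit together?** Independent generation and a double-blind design imply that the study team does not hold the key. The custody sentence says that two of its members keep the randomization. Followed literally, the plan leaves concealment and the blind of those two people unprotected.

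**The case against.** The strongest reply is that the text shows exposure and no actual breach. The product is stated to be coded and indistinguishable, and the clinical assessor is blinded. It is also unclear whether what is kept is a list of codes, the key to the codes, or both. All of this stands, and it limits the point to what is unprotected.

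A reader might infer three stronger things, none of which the protocol supports:

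- **That the double blind is broken or the label untrue.** Two people holding the list compromises their own blind. It does not by itself unblind patients or the assessor.
- **That the PI knows each next assignment while deciding eligibility.** No section gives the PI or the assistant that task, and certainty about the next assignment would require a list that shows the arm and is seen before enrolment.
- **That the list holders could stop recruitment on a favourable result and so inflate the false-positive rate.** The sample-size entry gives no number ("All Patients who presented to Gabra and Soba hospital and confirmed with COVID 19 during the study period will be included"), but it does bound recruitment by a study period. Dates for that period may stand in pages removed before review. No looks at results by arm are described. Error rates for repeated testing would therefore describe an assumed practice. They would not model the stated analysis either, which is a paired t test of baseline against post-treatment values. The absent sample size is a separate point.

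What survives the reply is the custody sentence itself. Coding protects only those who lack the key, and a blinded assessor does not cover enrolment or care.

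**Conclusion.** The point holds in its narrow form. The custody rule is inconsistent with independent generation and with the double-blind design, and it leaves allocation concealment and the blind of two study-team members unprotected. It should be corrected before the first assignment, because analysis cannot undo selection at entry.

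The size of any resulting bias cannot be derived from the protocol. It would depend on what exactly the two people hold and on what they do in the trial, and neither is stated. The exposure is greatest at entry and for improvement and discharge, and smaller for laboratory measurements. The conclusion rests on the text shown: a passage elsewhere that keeps the two holders out of enrolment, dispensing and care would reduce it.

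**What to change.** Replace the custody sentence in the section on randomization and blinding with wording such as:

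> The randomisation list and the code key are held only by the independent person who generated the sequence, or by another person with no role in enrolment, care, laboratory work or assessment. Coded packs are numbered in sequence within each centre and each age and sex stratum. The next pack is assigned only after consent has been given and eligibility confirmed. The PI, research assistants, treating staff, laboratory staff and assessors have no access to the list or key until the database is locked, except through individual emergency code-breaks, each of which is documented.

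The numbering has to run within centre and stratum. A single run of packs would lose the stratification that the protocol already specifies. The age bands need to be written down for this to work.

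The cost is a change of wording and of custody, with a small logistical burden on the independent person. That person is at present named only for generating the sequence and would now also oversee pack numbering (7 sachets a week for 4 weeks, so 7 × 4 = 28 per patient) and the emergency code-breaks. The change affects neither the treatments nor the outcomes nor the number of patients.

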**Gum Arabic administration:**

GA in powder form, it is a 100% natural extract powder produced mechanically from the wildy grown Acacia Senegal tree with a particle size less than 210 µm. The daily dose is 45 gram per day. It will be given in one sachet to be consumed in the early morning dissolved in 200 ml of water. The GA will be provided to the participants weekly for four weeks (7 sachets for each visit). Standardized questionnaire and check list will be used to collect data about patients' physical examination, weight, height, severity of the symptoms and any side effects. Gum Arabic will be purchased from nature gum company, Khartoum Sudan.

Placebo will be pectin one gram per day. It will be given in one sachet to be consumed in the early morning dissolved in 200 ml of water for 4 weeks.

**Investigations:**

The procedures for screening will be performed within one week before dosing, except where otherwise stated, and included the following:

- 1- Medical history,
- 2- Physical examination, including weight, height and vital signs.

3- The following routine laboratory tests: (A) CBC (B) serum chemistry

including renal function tests (RFT) and Liver function test (LFT)

**(serological tests)**

- i. **Real time PCR:** To determine the viral load
- ii. **Flowcytometry:** To measure the CD4 counts.
- iii. **ELISA for cytokines**

**Study protocols:**

Each patient will receive daily dose

The patients will be followed every week and the following investigation will be done during the visit for follow up: CBC, and urine analysis. LFT and RFT will be done weekly

Blood samples will be collected by certified nurse and will be used solely for the research purposes and will be destructed after completing the project.

**Primary outcome:**

Mean change from baseline score of Immune Response to end of the trial ( Time Frame: up to 4 weeks )

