#### **Specific objectives:**

- 1- To understand the immune response of disease progression and physiological pathway in patients consuming Gum Arabic (Acacia Senegal) for one month.
- 2- To study the innate and acquired mechanisms of defense against the coronavirus (cytokine and antibody responses) in placebo and experimental groups in each.
- 3- To assess clinical progression of the disease in group treated with Gum Arabic (Acacia Senegal)
- 4- Measure the level of anti-inflammatory marker (CRP & TNF $\alpha$ , IL6, IL10, IF $\gamma$ ) before and after GA ingestion

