## 5. Data analysis (Methods used for Data analysis)

**Data will be collected and coded and entered in excel sheet.**

SPSS .24 and Graph prism will be used. Paired *t* test will be used to determine statistical significance between baseline and post treatment results. *P* equal to or less than .05 will consider statistically significant. Data will be presented as means ( $\pm$ SD).

- **References:**

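### The only named test is a within-patient paired t test, so change from baseline in the primary outcome is neither compared between the randomized arms nor adjusted for baseline

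*Protocol*

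**What the plan says.** In section 4 (Methodology), the study is described as "Double blind, randomized placebo controlled clinical trial Phase III". The primary outcome is "Mean change from baseline score of Immune Response to end of the trial", with "Time Frame: up to 4 weeks". The score is not defined there.

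Section 5 (Data analysis) names the software, a significance threshold, presentation as means with SD, and one test. A paired t "test will be used to determine statistical significance between baseline and post treatment results", and P "equal to or less than .05 will consider statistically significant". It names no between-arm test, model or covariate, and it does not defer to another document.

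Specific objective 4 (section 3) also uses a before-after framing: inflammatory markers are measured "before and after GA ingestion". Specific objective 2 does mention both the placebo and the experimental group, but attaches no method of comparison.

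The Randomization and blinding text states that "laboratory and clinical assessments would be conducted at the baseline (after completion of informed consent), at first, second and 4th week". It does not itemise the markers, but objective 4 needs them at both ends of treatment. Stratification is on age and sex only.

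**The concern.** A randomized placebo-controlled trial learns the treatment effect from the difference between arms. A paired t test of baseline against follow-up instead asks whether patients changed. Newly diagnosed COVID-19 patients followed for four weeks may change substantially whatever they receive, so a significant fall in the Gum Arabic arm would not show that Gum Arabic caused it.

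The obvious repair, a two-sample comparison of raw change, would restore the arm contrast but leave a second weakness. Subtracting the baseline fully corrects for it only when the slope of the week-4 value on baseline is 1. The protocol's Scientific Background describes raised cytokines and C-reactive protein in infected patients, and many may have recovered by week 4, so a slope well below 1 is plausible. A raw change score would then be noisier than necessary, and an arm that happened to start higher would tend to show the larger fall. Randomization is not stratified on the baseline marker.

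**Working it through.** **Inputs.** From the protocol: two randomized arms, change from baseline to as late as 4 weeks, a paired t test, and a 0.05 threshold. Sidedness is not stated, so two-sided is assumed. The sample size is not a number but "All Patients who presented to Gabra and Soba hospital and confirmed with COVID 19 during the study period", subject to eligibility. No SD, effect size, power or correlation is given, so there is no planned figure to reproduce. Assumed below: 1:1 allocation, a common SD at both times, and baseline-to-week-4 correlation rho over a range.

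**1. The test as written.** Suppose it is run separately in each arm, both arms truly change by the same amount, and each test has power p. Then exactly one arm is significant with probability 2p(1-p), and Gum Arabic alone with probability p(1-p). At p = 0.5 these are 0.50 and 0.25. The pattern of within-arm P values is therefore no guide to a treatment effect.

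**2. Precision if the arms were compared.** In units of SD²:
- change score: variance 2(1-rho)
- ANCOVA on baseline: variance 1-rho²
- ratio: (1-rho²)/[2(1-rho)] = (1+rho)/2

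Power for ANCOVA where the change score has 80% is Phi[(1.960+0.842)·sqrt(2/(1+rho)) - 1.960]. The n per arm is for an assumed difference of 0.5 SD at 80% power.

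| rho | Change variance | ANCOVA variance | Ratio | ANCOVA power | n per arm, change vs ANCOVA |
|---|---|---|---|---|---|
| 0.3 | 1.40 | 0.91 | 0.65 | 93.5% | 88 vs 58 |
| 0.5 | 1.00 | 0.75 | 0.75 | 89.9% | 63 vs 48 |
| 0.7 | 0.60 | 0.51 | 0.85 | 86.0% | 38 vs 33 |

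**3. Chance baseline imbalance.** If the arms differ by d at baseline, the change-score contrast shifts by rho·d - d = -(1-rho)d, that is -0.7d, -0.5d and -0.3d at rho 0.3, 0.5 and 0.7. With an assumed 50 per arm, one standard error of imbalance is sqrt(2/50) = 0.20 SD. At rho 0.5 the shift is then 0.5 × 0.20 = 0.10 SD, in the direction opposite to the imbalance.

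**4. Simulation** (rho 0.5, 50 per arm, 20,000 runs). The slopes of the estimate on the imbalance were 0.50 for the week-4 value alone, -0.50 for change and 0.00 for ANCOVA. The variance ratio of ANCOVA to change was 0.76, against 0.75 from the formula.

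**5. Unequal SDs.** If the baseline SD is 1.5 times the week-4 SD and rho is 0.7 (both assumed), the change variance is 1 + 2.25 - 2(0.7)(1.5) = 1.15 and the ANCOVA variance is 1 - 0.49 = 0.51, in week-4 variance units. The ratio is 0.51/1.15 = 0.44, compared with 0.85 under equal SDs. The equal-SD figures are therefore illustrations, not estimates for this trial.

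**The case against.** The strongest reply is that the primary outcome text defines a quantity, not a model. ANCOVA on change gives the same treatment estimate as ANCOVA on the week-4 value, so the outcome as worded is compatible with baseline adjustment. Covariates are commonly settled in an SAP, and one may exist that is not shown here. Every number above rests on assumptions about rho, SD and sample size.

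Much of this stands. The primary outcome wording is not itself wrong, and a covariate merely left unnamed would be no finding. The problem lies in section 5, which does choose a method, and that method neither compares the arms nor uses baseline other than by subtraction.

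A reader might infer three stronger things that the documents do not support.
- The first is that a planned arm comparison is inefficient. No arm comparison is specified, so the precision loss applies only to the natural repair.
- The second is that a change score carries a chance baseline difference through whole. It leaves only the residual (1-rho)d, with reversed sign.
- The third is that comparing raw change would be biased or invalid. Under randomization it is unbiased on average, and the shift is conditional on an imbalance in the trial actually run.

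Adding a covariate also does not rescue a paired t test. The test itself has to be replaced.

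**Conclusion.** The point holds in this form. The defect in the text is that the stated analysis does not estimate the randomized treatment effect on the primary outcome. The lack of baseline adjustment is a secondary matter of efficiency, and it should be settled in the same edit, because a plain two-sample test on change would leave it in place.

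The size of the efficiency loss is conditional. With equal SDs, adjustment removes 35%, 25% or 15% of the change-score variance at rho 0.3, 0.5 or 0.7, and the gain shrinks towards nothing as rho approaches 1. Unequal SDs alter these percentages. With a linear relation and a common slope in both arms, the change score matches ANCOVA in large samples only if the slope on baseline is 1. The protocol supplies no value from which to choose within this range.

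**What to change.** In section 5, replace the paired t test as the primary analysis with a between-arm ANCOVA. The response is the week-4 value of the primary immune-response measure (or its change, since the treatment estimate is the same), with treatment arm and that measure's own baseline value as terms. Report the adjusted Gum Arabic minus placebo difference with a 95% CI. Apply the same model to each secondary marker with its own baseline, and keep within-arm change as description only.

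In the Primary outcome text, tie the immune response score to one named measure. Until that is done, no baseline value can be identified for the model. Naming one measure also avoids turning a single primary outcome into a set of marker tests.

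The cost is a few sentences of protocol text plus the decision on the measure. The model runs in the SPSS version already named. It needs no extra patients and no visits beyond the baseline and week-4 assessments already scheduled, provided the chosen measure is taken at both.

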## **Scientific Background:**

### **COVID 19 Pathogenesis:**

COVID 19 Coronavirus disease (COVID-19) is caused by SARS-COV2 and represents the causative agent of a potentially fatal disease that is of great global public health concern(1, 2).

Patients infected with COVID-19 showed higher leukocyte numbers, abnormal respiratory findings, and increased levels of plasma pro-inflammatory cytokines(1-3). Additionally, a value of 16.16 mg/L of blood C-reactive protein was noted which is above the normal range (0–10 mg/L)(2). Patients infected with COVID-19 showed higher leukocyte numbers, abnormal respiratory findings, and increased levels of plasma pro-inflammatory cytokines. Significantly high blood levels of cytokines and chemokines were noted in patients with COVID-19 infection that included IL1- $\beta$ , IL1RA, IL7, IL8, IL9, IL10, basic FGF2, GCSF, GMCSF, IFN $\gamma$ , IP10, MCP1, MIP1 $\alpha$ , MIP1 $\beta$ , PDGFB, TNF $\alpha$ , and VEGFA(1) The latest report shows the number of CD4+ and CD8+ T cells in the peripheral blood of SARS-CoV-2-infected patients significantly is reduced, Similarly, the acute phase response in patients with SARS-CoV is associated with severe decrease of CD4+ T and CD8+ T cells(3). The report in Lancet shows ARDS is the main death cause of COVID-19. Of the 41 SARS-CoV-2-infected patients admitted in the early stages of the outbreak, six died from ARDS(3). Main mechanism for ARDS is the cytokine storm, the deadly uncontrolled systemic inflammatory response resulting from the release of large amounts of pro-inflammatory cytokines (3).The cytokine storm will trigger a violent attack by the immune system to the body, cause ARDS and multiple organ failure, and finally lead to death in severe cases of SARS-CoV-2 infection(1, 2) . IFN-I(IFN- $\alpha$  and IFN- $\beta$ ) has a protective effect on SARS-CoV and MERS-CoV infection, but the IFN-I pathway is inhibited in infected mice(4). n Number of total T cells, CD4+ and CD8+ T cells were dramatically reduced in COVID-19 patients, especially among elderly patients ( $\geq 60$  years of age) and in patients requiring Intensive Care Unit (ICU)(3). Statistical analysis demonstrated that T cell numbers are negatively correlated to serum IL-6, IL-10 and TNF- $\alpha$  concentration, potential therapeutic targets preventing cytokine storm.

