#### **Gum Arabic as anti-inflammatory agent:**

Gum Arabic anti-inflammatory effect has been investigated in clinical trials (10,12). An anti-inflammatory effect of GA was demonstrated via the application of GA in drinking water given to rats with diabetes mellitus by a decrease of TNF $\alpha$  and IL-1 $\beta$  and increase of IL-10 (14).

Interestingly, Bovo et al. investigated the effect of GA on the complement system, as arabinogalactans are reported to be complement system modulators. The authors showed a pro-inflammatory activity of GA by activation of the classical and alternative pathways of the complement system (15). GA exerted local anti-inflammatory effects by modifying nuclear factor- $\kappa$ B (NF- $\kappa$ B) on the small intestine (12). In addition, a reduction of oxidative stress was shown after GA supplementation of drinking water in the liver tissue of rats with type I diabetes (16) and oral GA supplementation in humans suffering from sickle cell anemia (17). GA significantly increased oxidative burst/ROS production of bovine and human granulocytes in a dose-dependent manner (18,19). Similarly, arabinogalactan–protein (AGP) of GA may have pro-inflammatory properties on certain parts of the immune system(18, 20).

From all the above the main pathogenesis of COVID 19 is due to inflammatory process and cytokine storm. Gum Arabic is a prebiotic dietary fibers with proven anti-inflammatory properties and immunomodulatory agent. Nowadays, most of research have carried out on corona-virus are in the primary stages and the exact mechanisms remains unknown, infection spread and deaths are increasing in daily bases, the urge for vaccine and protective elements against the immunological response of the body against the virus is needed.

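### The primary outcome is the change in an immune-response score that nothing in the protocol produces, so the marker and its favourable direction can be chosen after the data are seen

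*Protocol*

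**What the plan says.** Section 4 of the Protocol, under Primary outcome, gives "Mean change from baseline score of Immune Response to end of the trial", with "Time Frame: up to 4 weeks". It is the only mention of such a score.

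The measurements appear elsewhere, one by one:

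- Objective 4 under Specific objectives reads "Measure the level of anti-inflammatory marker" and names five: CRP, TNF-alpha, IL-6, IL-10 and IFN-gamma.
- The serological tests under Investigations add viral load by PCR, flow cytometry "To measure the CD4 counts", and ELISA for cytokines that are not listed individually.

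The Data analysis section sets one threshold, P "equal to or less than .05 will consider statistically significant", and applies a paired t test to results that it does not identify.

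On IL-10, the COVID 19 Pathogenesis section lists it among the cytokines that are high in patients and reports that "T cell numbers are negatively correlated to serum IL-6, IL-10 and TNF"-alpha. The section on gum arabic as an anti-inflammatory agent cites a study in diabetic rats in which benefit was shown by lower TNF-alpha and IL-1 beta "and increase of IL-10 (14").

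**The concern.** A primary outcome has to be a quantity that can be computed from the data the trial collects, with the good direction known beforehand. Here the named quantity has no definition, and the data collected are five to seven separate laboratory values. Whoever analyses the trial must decide which value, or which combination, stands for the immune response, and whether a rise or a fall counts as benefit. The Justification section widens that choice, because it hopes both to strengthen natural immunity and to damp the cytokine storm. An immune response that goes up or one that goes down could each be reported as success.

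At stake is the trial's main claim. If the choice is made after results are visible, the nominal 5% error rate no longer describes it.

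**Working it through.** **1. Does anything in the protocol produce a score?**

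- Primary outcome: names a score; gives no components, scaling, weights, range or sign.
- Objective 4: five markers, none singled out, no rule for combining them.
- Serological tests: CD4 count and viral load, again separate. Viral load is a virological rather than strictly an immune measure.
- Gum Arabic administration: the questionnaire and checklist cover physical examination, weight, height, symptom severity and side effects. They do not measure immunity.
- Objective 2 mentions antibody responses, but no antibody assay is listed, so they are not counted here.

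Result: five candidates on the narrow count (objective 4), seven with CD4 and viral load, and no link from any of them to a score.

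**2. Is the favourable direction fixed?**

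Objective 4 labels all five markers anti-inflammatory, including CRP and TNF-alpha, so the label does not settle direction. For IL-10:

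- Pathogenesis section: raised in disease, and higher values go with fewer T cells. By implication a fall is good.
- Anti-inflammatory section: a rise in rats is offered as evidence of benefit. By implication a rise is good.

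No passage reconciles the two.

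**3. What would testing each marker cost in error rate?**

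The plan's only error figure is .05 per test. With one test, 1 − 0.95 = 0.05. No sample size, power or family-wise level is stated, so there is nothing further to reproduce.

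For k independent tests, the chance of at least one false positive is 1 − 0.95^k:

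- k = 5: 1 − 0.7738 = 0.226
- k = 6: 1 − 0.7351 = 0.265
- k = 7: 1 − 0.6983 = 0.302

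Cytokines are likely to be correlated, which lowers these figures. The documents give no correlations, so a common value r was assumed. Test statistics were simulated as Z_j = √r·g + √(1−r)·e_j with g and e_j standard normal (1,000,000 draws, two-sided .05):

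| Assumed r | 5 markers | 7 markers |
|---|---|---|
| 0 | 22.6% | 30.2% |
| 0.3 | 20.9% | 27.1% |
| 0.5 | 18.3% | 23.0% |
| 0.8 | 12.8% | 14.9% |

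The range is therefore about 13% to 30%. With one pre-specified marker, or one fully defined score, it returns to 5%.

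**4. Is the chosen marker certain to be measured at the end?**

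Randomization and blinding places laboratory assessments at baseline and at weeks 1, 2 and 4. The follow-up list under Study protocols contains blood count, urine analysis, and liver and renal function, but neither cytokines nor CD4. A week-4 cytokine measurement is implied by objective 4 and the visit times; it is not scheduled explicitly.

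**The case against.** The best defence is that a statistical analysis plan may exist and may hold a multiplicity rule, and that the single .05 threshold does not say that every marker will be tested. Both points are fair. The protocol does not state that each marker is tested at .05, and it cannot be said that selection will occur, only that nothing prevents it. The defence does not reach the core, however. What the primary outcome is, and which direction is favourable, belongs in the protocol, and this protocol fills that place with a quantity it cannot produce.

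Several stronger readings are tempting and are not supported:

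- *That the document states IL-10's good direction both ways.* It states neither. One side is a raised level and a correlation, the other a rat study. The Pathogenesis wording about therapeutic targets is loose, and the parallel sentence in the Introduction names T cells as the target, so no passage says that IL-10 should be lowered.
- *That IL-6 is listed among the raised cytokines, or has a uniquely clear direction.* The Pathogenesis list contains IL-10 and TNF-alpha but not IL-6. IL-6 rests on the same T-cell correlation as IL-10. TNF-alpha has rather more support in the text, being raised in disease and lowered by gum arabic in the cited rats.
- *That a summed score would lose signal by cancellation.* No passage proposes a sum, so no loss can be calculated.

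**Conclusion.** The concern holds. The primary hypothesis cannot be tested as written, because the score is undefined, no marker is designated in its place and no favourable direction is fixed. This follows from the text alone and needs no assumption.

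The error rate of about 13% to 30% is conditional. It assumes that five to seven markers are each tested two-sided at .05, that any one success would be claimed, and that each test is a valid comparison between arms. The high end needs independence and seven markers; the low end needs five markers and a correlation of 0.8. The five-marker case alone makes the point. The figure should not be read as the false-positive rate of the analysis described, since the only test named compares baseline with post-treatment values. Natural recovery could move that comparison without any treatment effect, which is a separate matter.

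**What to change.** Before any outcome data are seen by arm, replace the Primary outcome text with one of the following:

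- **One marker, one visit.** For example: *difference between arms in log IL-6 (or log TNF-alpha) at the 4-week visit, adjusted for baseline*. The choice of marker is the sponsor's.
- **A defined score.** State its components, the scaling of each, the weights and the sign, including the sign of IL-10 if it is a component.

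Then:

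- Add the chosen assay explicitly to the week-4 follow-up under Study protocols.
- Make all other markers, including CD4 and viral load, secondary with Holm adjustment. With one of seven as primary, six remain and the first Holm step is 0.05/6 = 0.0083.
- Report IL-10 two-sided, with no direction counted as success in advance.

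The deadline should be the first sight of outcome data by arm rather than formal unblinding, because the Randomization and blinding section has the principal investigator and a research assistant hold the allocation.

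The cost is protocol wording and a reconciled assay schedule; no new type of assay is needed. The small downside is that the other markers can no longer carry the primary claim.
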